## Abstract

**Background:**

Early childhood development is highly dependent on the sensitive care provided by caregivers, and interventions focused on supporting parents to improve their sensitivity have shown to be effective. The COVID-19 pandemic has had a significant impact on mental health, with pregnant women and mothers of infants being an especially vulnerable group and maternal sensitivity particularly affected. However, access to face-to-face interventions is restricted; thus, it is important to have remote interventions to support this group of mothers.

**Objective:**

The objective of this study is to evaluate the feasibility and acceptability of C@nnected, a group videoconferencing intervention to improve maternal sensitivity aimed at mother-infant dyads attending primary health care centers in vulnerable areas of Santiago, Chile.

**Methods:**

This is a randomized feasibility single-masked (outcome assessor) study with a qualitative component. It will involve a block randomization procedure to generate a 3:2 allocation ratio (with more people allocated to the intervention arm). The intervention consists of 4 group videoconferencing sessions adapted from a face-to-face intervention with proven effectiveness. The control group will receive treatment as usual, along with educational brochures. The feasibility and acceptability of this study will be quantitatively and qualitatively assessed. Changes in clinical outcomes relating to maternal sensitivity, depressive symptoms, postpartum maternal attachment, and infant socioemotional development will also be evaluated.

**Results:**

We finished adapting the face-to-face intervention to the videoconferencing format in July 2021. The study began recruitment in August 2021, and enrollment is expected to end in August 2022, with final study results expected in December 2022.

**Conclusions:**

This study will contribute evidence for the use of eHealth interventions to promote maternal sensitivity. It will also inform the design and implementation of a future randomized clinical trial.

**Trial Registration:**

ClinicalTrials.gov NCT04904861; https://clinicaltrials.gov/ct2/show/NCT04904861

**International Registered Report Identifier (IRRID):**

DERR1-10.2196/35881

## Introduction

### Background and Rationale

Ensuring adequate early childhood development is necessary for countries to move forward in an equitable and sustainable way; therefore, interventions to support early childhood development are essential to realize the United Nations Sustainable Development Goals [1]. The experience that best facilitates adequate child development is responsive caregiving provided by parents or primary caregivers [2], and one of the most relevant predictors of child development is the quality of the mother-child interaction [3]. The more sensitive, responsive, attentive, and cognitively stimulating the mother is, the better the results in her child. The main risk factors associated with the presence of low maternal sensitivity are maternal depression [4-6], low socioeconomic status, and other psychosocial risk factors [7], which are mediated by the high levels of stress experienced by these families [8].

Before 2020, mental health disorders were leading causes of global health-related burdens. With the emergence of the COVID-19 pandemic, mental health disorders have greatly increased across the world [9], especially in high-risk populations [10]. Pregnancy and postpartum are periods of special vulnerability for mental health. There are short- and long-term negative consequences to the physical, cognitive, and psychological development of children associated with prenatal and postpartum stress, anxiety, and depression [11], which are mainly due to a decrease in the quality of mother-child interactions. A recent Canadian study [12] carried out in pregnant women and those with children under 1 year of age showed an increase in anxiety symptoms from 29% to 72% after the COVID-19 pandemic and postpartum depression symptoms from 15% to 47%. The risk of mental health problems in pregnancy and the first year postpartum in the context of the pandemic has increased due to concerns related to the well-being of the child and aggravated by the consequences of preventive measures such as confinement, physical distance, reduced health checks, and difficulty obtaining support from the usual networks [13]. Moreover, these mental health problems are present at a greater extent in women of low socioeconomic status. Countries are recommended to implement mitigation strategies to reduce the mental health burden imposed by COVID-19, considering their local context and vulnerable populations [9].

For mothers to provide the responsive caregiving that their children need, they must have adequate mental health and a support network. Early interventions focused on supporting parents in providing responsive caregiving have proven to be effective [14-16]. Health services provide a critical starting point for these interventions, given their reach to pregnant women, families, and young children [16,17]. Thus, it is imperative to implement supportive interventions for pregnant and postpartum women that promote adequate sensitivity toward their children.

Global lockdown measures have disrupted routine health care for non–COVID-19 patients, so telemedicine has been escalated to reduce the risks of disease transmission [18]. Electronic mental health care is one of the most widely offered methods of health care, with evidence of applicability and efficacy in a wide range of formats [19]. A systematic review showed that group video conferencing interventions are feasible, improve access to health care, and have results similar to those obtained in face-to-face groups [20]. There is an interest in retaining or further incorporating virtual components devised in response to the COVID-19 pandemic into the standard delivery of interventions in the future [21]. In this context, it is important to implement remote interventions in primary health care (PHC) for mothers of children under 1 year of age that promote responsive caregiving.

### Chilean Context

Chile is a Latin American country that presents an important burden of mental health problems. The World Health Organization places Chile among the countries with the highest burden of morbidity from psychiatric diseases [22], and it has the world’s highest rates of postpartum depression [23,24] and preschool mental health problems [25]. Despite this, only 38.5% of those diagnosed receive some type of mental health service [22]. Chile has a comprehensive protection system for children from the prenatal period to 4 years of age known as Chile Crece Contigo (translated as “Chile Grows With You”) that aims to help all children reach their full potential for development through universal and targeted support services [26]; however, no specific interventions are offered to promote maternal sensitivity.

In 2 previous research projects, we developed and evaluated a face-to-face group intervention to promote maternal sensitivity during the child's first year of life [27]. The results, which will be published soon, showed positive effects on maternal sensitivity in mother-infant dyads attending PHC centers but low adherence rates. We also found a significant reduction in maternal depression symptoms and infant socioemotional development difficulties of resident dyads at Chilean female penitentiary centers [28].

### Objective

The primary aim of this paper is to report on the protocol comprising a pilot randomized feasibility trial to evaluate the feasibility and acceptability of C@nnected, a group videoconferencing intervention that aims to improve maternal sensitivity in mother-infant dyads attending PHC centers in Chile. Along with detailing the intervention, this paper provides an account of the plan to collect both quantitative and qualitative measurements of outcomes.

The secondary aims are to (1) to estimate the effect size in clinical outcomes between the groups after the intervention in terms of maternal sensitivity, postpartum depressive symptoms, postpartum attachment, and socioemotional development; and (2) identify the key parameters for the implementation and evaluation of the intervention, which will enable the design of an effectiveness study in the future.

## Methods

### Trial Design

This is a data analyst–blind, superiority, pilot feasibility study with a mixed design. The quantitative component is a 2-arm randomized parallel group of 50 mothers of infants aged 6-12 months who receive health care in 2 PHC centers in Santiago, Chile. Mothers will be randomized into the intervention or control group in a to 3:2 ratio (with more people allocated to the intervention arm). Both groups will receive the usual treatment and educational brochures provided by the PHC center, with the intervention group also receiving the C@nnected videoconferencing intervention. The qualitative component will consist of semistructured interviews with intervention providers to identify possible improvements and core components of the intervention as well as focus groups with mothers participating in the intervention to evaluate user acceptability and satisfaction with the implementation.

This type of study is suggested by the literature as an initial requirement for the implementation of an innovative intervention before applying it on a larger scale. It is also recommended to use quantitative and qualitative methodologies to evaluate feasibility and acceptability [29]. This clinical trial protocol follows the SPIRIT (Standard Protocol Items: Recommendations for Interventional Trials) and [30] and CONSORT (Consolidated Standards of Reporting Trials) guidelines [31]. Figure 1 provides a flowchart of the study process.

**Figure 1 figure1:**
[figure not shown]
Flowchart of participants. T0: preintervention assessment; T1: postintervention assessment.

### Study Setting

This study will be conducted at 2 PHC centers located in La Pintana and Puente Alto, 2 counties in Santiago, Chile, with low socioeconomic status. These counties have higher levels of poverty, overcrowding, and illiteracy than the national average.

### Eligibility Criteria

The population eligible for this study will be mothers with infants between 6 and 12 months of age attending either of the participating PHC centers. This age group was chosen because in the meta-analysis of the effectiveness of interventions to improve maternal sensitivity by Bakersman-Kranenburg et al [14], better results were observed with infants aged between 6 and 12 months than those under 6 months of age.

### Inclusion Criteria

The inclusion criteria are mothers of infants between 6 and 12 months who (1) attend 1 of the participating PHC centers, (2) are older than 18 years, (3) can speak Spanish fluently, and (4) have an electronic device that allows videoconferencing (ie, computer, tablet, or smart cell phone). In the case that a participant does not have internet access at home, we will consider supplying them with a prepaid card with internet gigabytes.

### Exclusion Criteria

The exclusion criteria are mothers with severe intellectual deficits or current psychotic symptoms and those participating in another early intervention at the PHC center.

### Interventions

#### Control Arm (Treatment as Usual Plus Educational Brochures)

Participants of this study are patients of the Chilean public health system and are supported by the Chile Crece Contigo national comprehensive child protection system. Some of the benefits are health checks during pregnancy, care during labor and delivery, child health checks, delivery of material for early stimulation, and detection and timely treatment of developmental delays [26].

In addition to receiving treatment as usual (TAU) at their PHC center, the control group will receive digital brochures with information on early parenting (once a week for 4 weeks). These brochures will summarize the content of each workshop session and the homework to be complete as a family. These are the same brochures handed out after each session in the intervention group.

#### Intervention Arm (TAU Plus C@nnected Group Videoconferencing Intervention)

The intervention group will participate in C@nnected, a group videoconferencing intervention adapted to the e-mental health format from a face-to-face brief attachment–based intervention that was previously designed, piloted [27], and evaluated through a randomized controlled trial (RCT) (results not yet published) to promote maternal sensitivity in mother-child dyads attending PHC centers. The face-to-face intervention was developed in 2012 following the framework proposed by the UK Medical Research Council for the development and evaluation of complex interventions [32] by the first 2 authors (VB and MO) of this study, considering the available evidence and local qualitative information. The core components obtained from the evidence were recommendations of the systematic review by Bakersman-Kranenburg et al [14] on effective interventions to improve parental sensitivity. The review shows that interventions that are carried out after 6 months of life, are of brief duration, and incorporate a second caregiver are more effective. From local qualitative research obtained through focus groups with both the possible users and providers of the intervention, different topics considered relevant by the participants and ideas on the best way to deliver the intervention were incorporated.

The general objective of the intervention is to enhance maternal sensitivity and promote skills in reading infant cues and responding sensitively, given that the inclusion of this variable in interventions, specifically in conditions of vulnerability, is associated with favorable results [33]. Each intervention session defines themes and objectives, worked through experiential activities, and immediately puts into practice the presented topics. In 1 of the sessions, another primary caregiver is actively invited to participate. At the end of each session, educational brochures with key concepts and homework are handed out to the participants to share and practice the new skills at home with the rest of the family**.**

The intervention is aimed at mother-infant dyads and consists of 4 sessions delivered over the course of 4 weeks, at 2 hours per week. Each group will include a minimum of 3 and a maximum of 6 dyads per group led by a trained provider. The activities are protocolized in a manual and are designed to be carried out with the infant. The manual specifies the structure and content of each session, the details of the materials to be used, relevant aspects to be emphasized during the activities, and additional information that delves more deeply into the issues addressed in the workshop. This aims to ensure the comprehensive replication of the intervention, which has been associated with the best effectiveness in this type of intervention [34]. Table 1 shows the main components of the intervention.

The adaptation to the video conferencing format was carried out between May and July 2021 by 2 authors of the face-to-face intervention in conjunction with a designer experienced with digital interventions. We used the recommendations of the Early Intervention Foundation [21] to achieve good results in virtual interventions as a frame of reference, which include the use of engagement elements and mechanisms to improve adherence and flexibility.

We reviewed the complete content of the workshop, adjusted the sessions to 1.5 hours, and adapted the training manual and all the activities for use in a web-based group environment. We aim to provide lighthearted and interactive activities to allow all participants to understand and share their experiences. In addition, we have included some activities associated with the impact of the COVID- 19 pandemic. Figure 2 is a screenshot showing an example of a videoconference session, and Figure 3 shows 4 examples of activities that will take place in the workshop.

**Table 1 table1:** Main components of the intervention with the objectives and activities of each session outlined.

Session	Name	Objectives	Examples of activities
1	“Knowing each other around attachment”	Achieve group cohesion Provide knowledge about attachment Recognize expected affective behaviors in an infant	Dynamics of presentation Difficulties in motherhood Common myths on attachment and parenting
2	“What does my baby need?”	Recognize crying as a signal of communication Recognize different expressions of emotions in babies Understand importance of responding to infant's needs	Recognize sensitive responses in caregivers Work with different emotions and expressions in infants
3	“Massages and agreements in parenting style” (Another relevant caregiver is invited)	Work on parental sensitivity through massage Involve another caregiver in the concept of attachment Achieve consensus among caregivers in some relevant issues of parenting	Infant massage with emphasis on sensitive interaction Watch locally made videos showing different parenting situations (eg, infant´s signs, safe exploration, talking and reading to children, and challenges in parenting)
4	“Boundaries and positive parenting”	Understand the importance of setting boundaries with respect and love Have strategies to set boundaries Resolve doubts regarding child abuse Recognize behaviors associated with positive parenting Know children's rights	Invent a story from an image that shows a difficulty in parenting Comment on experiences related to child abuse Express any doubts regarding the proper way to treat children Provide reflections on children's rights

**Figure 2 figure2:**
[figure not shown]
Screenshot of a videoconference session.

**Figure 3 figure3:**
[figure not shown]
Screenshots illustrating different intervention activities. (A) Common myths in attachment and parenting; (B) working with different emotions and expressions in infants; (C) watching videos showing different parenting situations; (D) inventing a story from an image that shows the challenges of parenting.

In this study, each workshop will be led by a provider who is also a psychologist. Before conducting the intervention, the providers will receive a half-day training from the authors of the intervention. The video conferences will be recorded to guarantee the fidelity of the intervention and used later to perform a qualitative analysis of the change process [35].

To ensure internet connection during the evaluations and videoconferencing sessions, participants who do not have regular internet access will receive a prepaid card with internet gigabytes. To improve adherence to video conferencing sessions, the participating mothers will agree on the most convenient day and time for them to be held. In addition, a telephone chat group will be created to remind participants of the upcoming session and homework 1 day prior. If a participant cannot attend a videoconference session, they will be contacted by telephone by the provider to summarize the most important information of the session. This call will last between 15 and 20 minutes, and the main ideas and content of the session will be discussed, reinforcing the importance of positive interactions between mother and baby, sensitive care, and participation in the subsequent group sessions. For each participant to be considered to have received the intervention, they must attend at least 2 group videoconference sessions and 2 telephone calls or attend at least 3 of the 4 group video conference sessions.

### Outcome Measures

#### Primary Outcome Measures

The primary outcome measures are listed as follows.

#### Feasibility of the Intervention

Feasibility will be evaluated in terms of the following factors: (1) eligibility rates, referring to the proportion of mothers who meet inclusion criteria compared with the total number of mothers contacted by telephone; (2) recruitment rates, meaning the proportion of mothers who accept the invitation to participate in the study with respect to those who meet eligibility criteria; (3) adherence to group intervention, meaning the proportion of participating mothers in the intervention arm that receive the intervention (at least 2 group video conference sessions plus 2 telephone calls) and the average number of online sessions attended; and (4) follow-up rates by treatment condition, which refers to the proportion of participants that completed the postintervention assessment

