## Discussion

### Expected Findings

The objective of this study is to assess the feasibility and acceptability of the C@nnected group videoconferencing intervention, which aims to improve maternal sensitivity in mother-infant dyads attending PHC centers in Chile and was adapted from a face-to-face intervention. We expect to find an adequate feasibility of this intervention in terms of achieving good recruitment rates (around 60% mothers will accept the invitation to participate in the study with respect to those who meet eligibility criteria), good adherence to group intervention (around 60% in the intervention arm will receive the intervention), and adequate adherence to the sessions (the average expected attendance is 3 out of 4 sessions). We expect to find a very good acceptability of the intervention with high scores in the satisfaction questionnaire and positive evaluation in the qualitative assessment. We also expect to find favorable results of the intervention in terms of clinical outcomes, especially relating to maternal sensitivity, which will allow us to estimate the sample size for the future RCT to evaluate effectiveness. The results of this study will inform the key parameters for the implementation and evaluation of the intervention and facilitate the design of an effectiveness study in the future.

The COVID- 19 pandemic has led health teams to adapt some interventions to the eHealth format, and it is likely that many of these interventions will remain in this format even after the pandemic is over. Nevertheless, we should not assume that interventions will work equally as well when delivered through virtual methods. Existing interventions must be carefully adapted and include a focus on identifying the core components that must be maintained [21].

Internationally, there are some group parenting interventions with proven efficacy to increase maternal sensitivity; however, one of the main problems of this type of intervention is low adherence [48]. The development of eHealth interventions may improve the accessibility and flexibility of group-based interventions, which are important for parents. If this group intervention delivered by videoconference is shown to be feasible, it will be particularly useful for mothers that face barriers to attending face-to-face interventions.

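### The primary outcome labelled adherence to the group intervention is a receipt rate that mixes group attendance with telephone make-up, and its two definitions disagree

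*Protocol article*

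**What the plan says.** The Intervention Arm section (text after Figure 3) describes a make-up call: "If a participant cannot attend a videoconference session, they will be contacted by telephone by the provider to summarize the most important information". On its length: "This call will last between 15 and 20 minutes". It then gives the receipt rule: "they must attend at least 2 group videoconference sessions and 2 telephone calls or attend at least 3 of the 4 group video conference sessions".

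The section Feasibility of the Intervention gives its third factor as "adherence to group intervention, meaning the proportion of participating mothers in the intervention arm that receive the intervention". The gloss on receipt, and what the factor adds after it, read: "receive the intervention (at least 2 group video conference sessions plus 2 telephone calls) and the average number of online sessions attended". The factor thus has two components, a proportion and a mean. The gloss on the proportion gives only the route with two sessions and two calls.

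Expected Findings attaches an expectation to each component: "good adherence to group intervention (around 60% in the intervention arm will receive the intervention"), and average attendance of 3 of the 4 sessions.

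**The concern.** The label speaks of the group, but the proportion measures receipt. The provider makes a call because the mother was absent, so a completed call records the provider's follow-up and the mother's availability by telephone. It does not record use of the group videoconference.

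This matters because the trial asks whether a group videoconferencing format is feasible. The article reports low adherence to the face-to-face version (Chilean Context). It also names low adherence as a main problem of group parenting programmes and suggests that eHealth delivery may improve accessibility and flexibility (Expected Findings). A composite rate cannot test that suggestion cleanly, and planners of the later effectiveness trial could read it as group attendance.

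The second problem lies in the definition itself. The outcome section and the Intervention Arm section give different receipt rules, so the primary proportion has two possible values.

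**Working it through.** The article derives no figure here that could be reproduced; the 60% and the 3 of 4 sessions are stated expectations.

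**Inputs.** Total sample 50 (Sample Size). Allocation 3:2 (Sequence Generation). Four sessions (Intervention Arm). Expected receipt about 60% (Expected Findings). The intervention arm has 50 × 3/5 = 30 mothers, and 60% of 30 = 18.

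**Step 1: the two receipt rules.** Calls are described only for missed sessions, so a mother attending *k* of 4 sessions can have at most 4 − *k* make-up calls.

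| Sessions attended | Most calls possible | Intervention Arm rule | Outcome section, read literally |
|---|---|---|---|
| 4 | 0 | received | not counted |
| 3 | 1 | received | not counted |
| 2 | 2 | received if both calls are made | counted if both calls are made |
| 0 or 1 | 4 or 3 | not received | not counted |

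Read literally, the outcome section counts only mothers who missed exactly half the sessions.

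**Step 2: do receipt and the mean together give the proportion attending most sessions?** Take the Intervention Arm rule and assume that every missed session is followed by a completed call. Receipt then means at least 2 sessions, and non-recipients attended 0 or 1. Fix receipt at 18/30 and the mean at 2.0, that is, 60 attendances in total.

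- Scenario A: 6 mothers attend 4, 12 attend 2, 12 attend 1. Total 24 + 24 + 12 = 60. At least 3 sessions: 6/30 = 20%.
- Scenario B: 18 attend 3, 6 attend 1, 6 attend 0. Total 54 + 6 + 0 = 60. At least 3 sessions: 18/30 = 60%.

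These are the exact limits. Only the 18 recipients can reach 3 sessions, which gives the maximum. For the minimum, the 12 non-recipients supply at most 12 attendances, so the recipients need at least 48. That is 12 above the 36 they have at two sessions each, and each mother can add at most 2, so at least 6 must exceed two sessions. Both reported figures are identical in A and B, and no attendance model is needed. Under the literal outcome-section gloss, A would score 12/30 = 40% and B 0/30.

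**Step 3: how large might the gap be?** The gap between receipt and attending at least 3 sessions is P(exactly 2 of 4). The attendance probabilities below are assumptions, not figures from the article. With independent attendance, P(X ≥ j) comes from Binomial(4, p) with p = mean/4. With within-mother correlation 0.2 or 0.4, a beta-binomial with the same mean is used.

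| Mean sessions | Correlation | P(≥2), receipt | P(≥3) | Gap, points |
|---|---|---|---|---|
| 2.0 | 0 | 68.8% | 31.3% | 37.5 |
| 2.0 | 0.2 | 62.9% | 37.1% | 25.7 |
| 2.0 | 0.4 | 58.8% | 41.3% | 17.5 |
| 2.4 | 0 | 82.1% | 47.5% | 34.6 |
| 2.4 | 0.2 | 74.7% | 50.4% | 24.2 |
| 2.4 | 0.4 | 69.6% | 52.9% | 16.7 |
| 3.0 | 0 | 94.9% | 73.8% | 21.1 |
| 3.0 | 0.2 | 88.6% | 71.4% | 17.1 |
| 3.0 | 0.4 | 83.7% | 71.2% | 12.5 |

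Receipt of exactly 60% is reached at means of 1.78, 1.91 and 2.04 sessions (correlation 0, 0.2, 0.4), with 23%, 34% and 43% attending at least 3.

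**Step 4: contact time.** Two calls give 2 × 15–20 = 30–40 minutes. Two missed sessions amount to 2 × 1.5–2 hours = 3–4 hours; the Intervention Arm section gives both session lengths.

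**The case against.** The strongest reply is that group uptake is already measured. The same primary outcome continues with "and the average number of online sessions attended", which gives calls no credit and has its own expected value. A low group uptake behind a 60% receipt rate would show there: in Step 3 it occurs at means of about 1.8 to 2.0, well below the expected 3. At the expected mean of 3.0, the stricter proportion is 71% to 74% under all three models, so it too exceeds 60%. This stands, and it limits the harm. It does not remove the gap, because Step 2 shows that the mean and the receipt rate together leave the proportion open.

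A reader might infer that the rate says nothing about uptake of the group format. The documents do not support that: two group sessions are always required, and calls alone never qualify. A reader might also infer that the 60% is a hurdle that telephone calls could help the trial clear. It is an expectation in the discussion, not a progression criterion, and the article already words it as receipt.

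Counting make-up calls as receipt is an openly declared design choice, and this point does not dispute it. Nor can one say flatly that the planned rate overstates group adherence: under the literal outcome-section gloss, which drops mothers with 3 or 4 sessions, it could understate it.

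A fuller protocol might hold an attendance breakdown. That would supply the extra proportion, but it would not cure the label or the disagreement within the article.

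**Conclusion.** The point holds as a weakness of labelling and definition in a primary feasibility outcome. The proportion is receipt, combining group attendance with telephone make-up. Adding the mean shows average group uptake but not how many mothers attended most sessions.

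The 20% to 60% range is exact for 18 of 30 receiving, a mean of 2.0 and a completed call after every missed session. The gap of 12.5 to 37.5 points rests on that same call assumption and on assumed means of 2.0 to 3.0 sessions with correlation 0 to 0.4. The article supports only the mean of 3.0, as an expectation, where the gap is 12.5 to 21.1 points. If some calls fail, some mothers with two sessions drop out of receipt and the gap shrinks.

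The disagreement between the two receipt definitions needs only the article's statement that calls follow missed sessions.

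**What to change.** In Feasibility of the Intervention, keep the mean number of online sessions and report two proportions of the intervention arm beside it:

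- (a) adherence to the group format: attended at least 3 of the 4 group sessions, telephone calls not counted;
- (b) receipt of the intervention: the Intervention Arm rule, stated once and identically in both sections after they are reconciled.

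In Expected Findings, label the 60% as expected receipt (b), and base statements about adherence to the group format on (a) and the mean. The make-up calls and the receipt rule itself need no change.

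The cost is a wording change and one more descriptive proportion. No new data should be needed: the mean already requires session counts, and the receipt rule implies that calls are recorded per mother, although the article does not say so. The drawback is that the group-adherence figure will be lower than receipt whenever some mothers qualify through calls.
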